## **B. STUDY DESIGN AND POPULATION**

### **B1. Overview or Design Summary**

Study design: Longitudinal observational follow-up study.

Trial Site. The study will be conducted at Lira Medical Centre (LMC, Lira, Uganda) in collaboration with Med Biotech Laboratories (MBL). LMC has been the site of the BK-SE36 trial and MBL has been the collaborating institution and local counterpart in Uganda. Lira Medical Centre (LMC) has been chosen as the trial site based on infrastructure, logistics and the standard health care it provides to the community and neighboring counties. The Centre itself is readily accessible by foot or ground vehicle to all perspective trial volunteers. It has an outpatient and inpatient facility, surgical theatres, has a clinical laboratory equipped to carry out basic laboratory assays (blood counts and serum

chemistries), a pharmacy, and is staffed 24 hours/day and 7 days/week. At present, the Centre is the primary provider of medical care in Lira and neighboring towns since its establishment in 2005. As a private, non-governmental organization hospital the Centre provides care free-of-charge to the community for immunization, tuberculosis drugs, blood transfusion, ante-natal care and counseling, routine malaria check for pregnant women, mosquito bednets and vitamins. For the clinical trial of Phase 1b, the whole third floor of the hospital building was renovated to include blood collection rooms, pharmacy, three private consultation rooms, waiting and observation area, vaccination room, storage and administrative space. During the clinical trial, the trial floor operated 24 h a day, 7 days a week. The team has been trained to conduct GCP-compliant studies, using source documents, written informed consent and standardized case report forms. The trial team has also been establishing a strong trust and rapport with the community, enhancing the local capacity of the community as well as being a health care provider to volunteers. The site is connected to MBL Laboratories in Kampala, Quintiles services in South Africa, Kenya, Dublin and to the sponsor via a VSAT system, which also allows faster communication links and the Internet.

## **B2. Study Population/Eligibility Criteria:**

### **Background Intervention of target population:**

B2.1 BK-SE36 treated cohorts: 2 dose arms (full- and half-dose); doses administered twice at 21-day interval

B2.2 Placebo treated cohorts: 2 dose arms (0.5 and 1.0mL of physiological saline); doses administered twice at 21-day interval

B2.1 and C2.2 are subjects of the Stage2 BK-SE36 Phase1b trial who will be followed-up for antibody titers and malaria infection incidences.

B2.3 Control group: no intervention [This is equivalent to placebo-treated cohorts. Due to the length of follow-up and the possibility of subject drop-out, additional subjects are needed for comparison to BK-SE36 cohorts]. To serve as appropriate control group (taking into consideration that an almost equal opportunity for malaria infection should occur between cohorts), the inclusion and exclusion criteria for the BKSE36 malaria vaccine Stage2 study applies:

*[Inclusion criteria 2]: Stage2, 6 to 20 y old*

Healthy subjects are specified, and the inclusion criteria of malnutrition index and laboratory test values were included to reduce individual variation.

- <2.1> Volunteers, irrespective of gender, aged 6 to 20 years (age on informed consent)
- <2.2> Those who do not suffer from severe malnutrition, whose BMI is between 5th percentile to less than the 85th percentile for 6-19 y old; and between 18.5-25.0 for 20 y old;
- <2.3> Those who can give affirmative agreement to participate in the trial. For children between 8 to 17 y, the child's assent takes precedence over the parent(s)/guardian(s) consent.
- <2.4> Those who are able to agree, comply with matters to be observed during participation in the trial, undergo consultation/examination, as described in this protocol, and report symptoms;
- <2.5> Those who are considered to be eligible to participate in this trial based on screening:
  - <2.5.1> Vital signs and physical examination are within baseline range
  - <2.5.2> Hematology: Within 25% deviations from the upper and lower limits of the baseline range. The differential white blood count is not questioned when the white blood cell count is within the

baseline range.

<2.5.3> Blood chemistry:

- AST, ALT, and creatinine: Within the baseline range
- Total bilirubin: Within 50% deviation from the upper limit.
- Serum electrolytes: Within the baseline range
- Other blood chemistry items: Within 25% deviation from the upper and lower limits of the baseline range.

<2.5.4> Urinalysis: Within the normal range

*[Exclusion criteria 2]:*

Any subject meeting any of the exclusion criteria at baseline will be excluded from trial participation.

- <1> Persons with fever (37.5°C or higher) on administration of the test vaccine;
- <2> Persons with a clear history of food/drug-related anaphylaxis;
- <3> Females (adolescents/adults) who are pregnant or have a positive urine  $\beta$ -hCG on the day of, or prior to, administration;
- <4> Females currently lactating or breast-feeding;
- <5> Persons with acute or chronic cardiovascular, pulmonary, hepatic, renal, or neurological condition, which in the opinion of the investigator may increase the risk of the subject from participating in the trial;
- <6> Persons with a history of fever within 2 days after preventive administration with other types of vaccine, or those in whom symptoms have suggested systemic allergy;
- <7> Persons with a history of convulsion other than febrile convulsions in malaria in the past 6 months to 1 year
- <8> Persons with any confirmed or suspected immunosuppressive or immunodeficient condition, including human immunodeficiency virus (HIV) infection. (No infectious disease testing will be conducted. HIV testing will not be done. Severe, suspected infectious diseases will be ruled out by investigators during physical examination/consultation, blood hematology/chemistry tests; although not conclusive of the causative agent.);  
Additional oral confirmation: Subject informed the investigator that he/she has been tested positive for HIV/AIDS. (Information on the child's HIV status could be obtained from their parents or guardians.)
- <9> Persons with a history or tentative diagnosis of drug allergy; especially to common drugs like penicillin, sulphonamides, etc.
- <10> Persons with (history of) chronic alcohol consumption and/or illicit drug use;
- <11> Persons who took any medication within 1 week before administration of this test vaccine (except for artemether/lumefantrine and dihydroartemisinin-piperaquine);
- <12> Persons to whom any live vaccine was administered within 4 weeks before administration of this test vaccine, or inactivated vaccine/toxoid was administered within 1 week;
- <13> Persons who participated in another trial within 4 months before administration of this test vaccine; or simultaneous participation in any other clinical trial;
- <14> Persons in whom 200 ml of blood was collected (donation) within 1 month before administration of this test vaccine, or more than 400 ml of blood was collected within 3 months;
- <15> Persons who have recently undergone blood transfusion in the last 3 months.
- <16> Others who are not considered to be eligible by the investigator or those, whose medical condition would, in the opinion of the investigator, make the subject unsuitable for the trial.

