### 3. Outcome:

**1)** antibody response as a result of natural malaria infections; **2)** malaria incidence; **3)** treatment incidence density (treatments per time at risk); **4)** prevalence of malaria parasitemia and parasite density for each group that received BK-SE36 vaccine (at half or full dose) and those who received placebo or no administration (control group); **5)** change in antibody titres/epitope recognition against synthetic short peptides *spanning the whole length of SE36*.

**4. Study site:** Lira Medical Centre (LMC), Lira, Uganda

**5. Study design:** Longitudinal observational study in children who participated in the BK-SE36 malaria vaccine trial in Uganda.

**6. Participants:** BK-SE36 Phase1b Stage2 study subjects (6-20 y old) who give consent for additional 11 months follow-up period, AND additional volunteers for recruitment to achieve an equal number of subjects in the control group (*i.e.* BK-SE36 cohort ( $n=66$ ) = placebo cohort + *additional volunteers* ( $n=66$ )). These additional volunteers that did not participate in Phase 1b Stage2 trial will not be receiving any intervention/administration.

**7. Number of participants:** A total of 132 participants.

(33) subjects = administered with half dose SE36 (50 µg)

(33) subjects= administered with full dose SE36 (100µg)

(9) subjects = administered with half dose of placebo (0.5mL physiological saline)

(9) subjects = administered with full dose of placebo (1.0mL physiological saline)

(48) additional volunteers to be recruited into the control group (no administration)

**8. Expected start date:** End of 40 days surveillance period of Phase 1b, Stage2

**9. Primary completion date:** 11-months after study start

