***Plasmodium falciparum* and Malaria Vaccine Candidates.** *P. falciparum*, responsible for the majority of malaria deaths, is a multistage parasite invoking stage-specific host immune responses. To date, the approach to malaria vaccine development has primarily concentrated on eliciting these stage-specific immune responses. Thus, malaria vaccine candidates can be divided into (1) those that stimulate a pre-erythrocytic (sporozoite or liver) immune response, (2) those that block malaria transmission by promoting an antibody response against antigens expressed in the sexual stage within the midgut of the mosquito, (3) those that target the asexual blood stages of the parasite, with vaccines reducing the toxic effect of the infection.

Natural immunity against malaria appears to be acquired over time, requires multiple infective bites, and is lost in the absence of continued exposure. The goal of blood stage malaria vaccines is to protect against disease and death, which can be achieved through acquisition of such immunity. In spite of tremendous efforts to develop malaria vaccines for decades, an effective vaccine is not yet available.

**The Malaria Vaccine Candidate BK-SE36.** It has been demonstrated that recombinant N-terminal domain of *P. falciparum* serine repeat antigen 5 (SERA5), SE36, is a potential erythrocyte stage malaria vaccine candidate [15]. Previous immuno-epidemiological studies in Apac show that natural antibody responses to SE36 are widespread and age-dependent with adult population roughly divided into two categories: sero-positive or sero-negative to SE36 antigen. An epidemiological study in malaria patients from holo-endemic Solomon Islands suggests that there is significant correlation between lower parasitemias and higher IgG titers against SE36. An experimental study using squirrel monkeys demonstrated that vaccination with SE36 protein and aluminum hydroxide conferred protection against high parasitemia and boosted serum anti-SE36 IgG after *P. falciparum* challenge. The challenge infection also changed the epitope recognition of anti-SE36 IgG to a recognition pattern similar to those observed in people with naturally acquired immunity. In chimpanzees, SE36 plus alum was highly immunogenic with antibody titers lasting more than a year. These observations provided the impetus for the development of BK-SE36 as a malaria vaccine [15].

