#### At each monthly visit:

- 1 Consultation/examination of injection site (for administered subjects) if there are unresolved AEs
- 2 Consultation interview for recent illness, malaria symptoms; includes capturing malaria incidences between visits
- 3 Vital signs (temperature, blood pressure, pulse rate)
- 4 A few drops of blood sampling (by finger prick) for malaria smear, filter paper blots, and ELISA assay.
5. Blood draw (4 mls) of venous blood for serum sampling

Subjects will be assigned to fall into different consultation days. Clinic visits will be in groups. Care should be exercised whenever possible that the BK-SE36 administered cohort group can be matched to a control cohort group in the same locality for equal "bias" in malaria incidence rates.

During this follow-up period, adverse events will not be reported but malaria episodes will be documented and blood samples collected for immunological testing. Daily body temperature monitoring and recording by participants or parents /guardians will be carried out by the participants themselves at home throughout the study period. Training of participants and /or parents/guardians in the use of thermometers, reading and recording of body temperatures will be conducted during the start of the study

At the final visit:

Blood sampling (20-ml venous blood) for ADCl and ELISA assays

Passive follow-up for malaria will consist of visits to LMC trial site whenever the subject is sick. During each visit, the subject will be evaluated and a malaria smear will be done whenever malaria is suspected. During the course of evaluation for malaria, other illnesses maybe uncovered in the study subjects, such as upper respiratory infections, and other bacterial or viral infections. The pharmacy can provide subjects with common over-the-counter analgesics such as paracetamol as well as antibiotics for the treatment of minor ailments and infections. If further evaluation or treatment is necessary, the subject will be referred to the hospital arm in LMC.

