**E. Statistical considerations**

The purpose of this study is to estimate malaria episodes, patterns of immune responses as well as compare these rates and patterns in different doses/interventions of the study based on the Phase 1b, stage2 protocol. Listings will show all observed data. Should there be a need for early termination of the study, available data will be analyzed and interpreted in light of early termination.

To assess and compare the duration of specific antibody response to SE-36 over a 11 month period:

1. A test will be performed to check for any significant differences in the antibody concentrations of the two dose groups.

2. Immunogenicity responses by vaccine and dose group will be described over time. Individual responses can also be described over time and stratified by dose cohort.
3. For antibody concentrations measured, a longitudinal model will be built to describe the antibody response over time. The model will also explore if there are any differences between the two doses used for Stage2.
4. Waning will be assessed by comparing levels of antibody with time, as well as malaria infection.
5. Average parasitemia in all samples collected during the whole period will be compared between the vaccine and placebo group (including number of incidences of mild and severe malaria in BK-SE36 vs. control groups). Kaplan-Myer plots will be used to compare the immunological protection between blood parasitemia levels and administration of BK-SE36

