| Medical History                                                                                                                                                                                                                                                                                                                                                                                                                                                                                                                                                                                                                                                                                          |
| 1. Malaria history from last visit:  None  Yes (date)_____
1.1 Are there other household members who are suffering from malaria?
 None  Yes,( number)_____
1.2 Use of mosquito bednet while sleeping:  No  Yes
1.3 Was the mosquito net used soaked or treated with an insecticide to kill or repel mosquitoes?
 No  Yes
1.4 Has anyone sprayed the interior of the house against mosquitoes?  No  Yes                                        |
| 2. No of days symptomatic before diagnosis was made:  Not known  _____ days                                                                                                                                                                                                                                                                                                                                                                                                                                                                                                                                                                                     |

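### Of the 66 controls, 48 are untreated volunteers from outside the Stage 2 trial, called equivalent to placebo on grounds of numbers alone, and the malaria comparator is named in two ways

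*Protocol*

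**What the plan says.** Synopsis items 6 and 7 build two groups of 66. The vaccine group is 33 half-dose and 33 full-dose subjects. The control group is 9 + 9 Stage 2 placebo subjects plus volunteers who were not in that trial: "48) additional volunteers to be recruited into the control group (no administration". Section B2.3 says of the no-intervention group: "This is equivalent to placebo-treated cohorts. Due to the length of follow-up and the possibility of subject drop-out, additional subjects are needed". Section C(ii) recruits these volunteers after Visit 10, during the 40-day passive surveillance.

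Several provisions aim at comparability:
- B2.3 applies the Stage 2 inclusion and exclusion criteria, so that exposure to malaria is nearly equal.
- C(i) makes the residence of consenting trial subjects a consideration when controls are screened.
- C(ii) wants the volunteers to represent the consenting subjects, without naming variables.
- Section D asks for care, as far as possible, that the "BK-SE36 administered cohort group can be matched to a control cohort group in the same locality".

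Objective b and hypothesis 3 set vaccinees against placebo and untreated subjects together. A3.2 describes the comparison of infection rates and severity as baseline data on vaccine efficacy. A4.1 lists parasitaemia rates, malaria incidence and treatment incidence density as primary endpoints.

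Section E item 5 says that average parasitaemia "will be compared between the vaccine and placebo group". The same sentence adds, in brackets, "including number of incidences of mild and severe malaria in BK-SE36 vs. control groups". Kaplan-Meier plots follow. No covariate is mentioned in that item.

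**The concern.** The justification in B2.3 (long follow-up, possible drop-out) explains why more controls are wanted. It does not show that people from outside the trial have the same malaria risk as people inside it.

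There are reasons to expect differences:
- The volunteers enter after Stage 2 dosing. They have a smear at screening, and relevant findings are treated or referred. The Stage 2 subjects passed the same criteria before two doses given 21 days apart.
- Several exclusion criteria are timed to administration of the test vaccine, which the volunteers never receive, so the same criteria do not give the same baseline.
- The volunteers know that they received nothing. Episodes between visits are found by interview and by self-initiated attendance, which depend on reporting and care-seeking.
- Section A1 says that "natural antibody responses to SE36 are widespread and age-dependent" and that symptomatic malaria becomes less frequent as children grow older. Yet age is only restricted to 6-20 years; it is not balanced.

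Any of these can create or hide an apparent vaccine effect on primary endpoints. The wording of item 5 adds a second problem, because the comparator for those endpoints is not fixed.

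**Working it through.** **Group sizes (Synopsis item 7).** Vaccine: 33 + 33 = 66. Control: 9 + 9 + 48 = 66. Total: 66 + 66 = 132, which reproduces the stated figure. Share of controls from outside the trial: 48/66 = 0.727, or 73%.

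**Comparator.** In item 5, the placebo group could mean the 18 Stage 2 placebo subjects or serve as loose wording for all controls. The term control group covers all 66 in the Synopsis, but in B2.3 it heads the no-intervention volunteers alone, that is 48. The documents do not settle which is meant for which endpoint.

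**Size of possible bias.** The protocol gives no malaria rates, so the following ratios are assumptions. Let the trial cohort, vaccinated or placebo, have rate 1 (no vaccine effect) and the 48 volunteers rate r. Then:

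- pooled control rate = (18 + 48r)/66
- apparent efficacy = 1 - 66/(18 + 48r)

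| r | 18 + 48r | Apparent rate ratio | Apparent efficacy |
|---|---|---|---|
| 1.10 | 70.8 | 0.932 | 7% |
| 1.25 | 78 | 0.846 | 15% |
| 1.50 | 90 | 0.733 | 27% |
| 0.90 | 61.2 | 1.078 | -8% |
| 0.75 | 54 | 1.222 | -22% |
| 0.50 | 42 | 1.571 | -57% |

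The effect is not symmetric: a lower rate in the volunteers distorts the estimate more than an equally higher one.

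**Precision of the contrasts that separate the two kinds of control.** With equal variance, the standard error of a difference in means is proportional to sqrt(1/n1 + 1/n2).

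- 66 v 66: sqrt(2/66) = 0.1741
- 66 v 18: sqrt(1/66 + 1/18) = 0.2659, ratio 0.2659/0.1741 = 1.53
- 18 v 48: sqrt(1/18 + 1/48) = 0.2764, ratio 0.2764/0.1741 = 1.59

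Illustrative power at two-sided 5%, for an assumed risk ratio of 0.5:

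| Assumed control risk | 66 v 66 | 66 v 18 |
|---|---|---|
| 0.3 | 0.54 | 0.33 |
| 0.5 | 0.85 | 0.53 |
| 0.7 | 0.99 | 0.77 |

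The placebo-only contrast is therefore useful beside the pooled one, but weak as a replacement.

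**Information already at hand.** Age is an eligibility item. Residence is noted at consent and on the visit questionnaire (Section N). The questionnaire also asks about "Use of mosquito bednet while sleeping", insecticide treatment of the net and spraying of the house.

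**The case against.** The strongest reply is that Section E is an outline. It forbids no covariate, and a separate analysis plan, not shown here, may name them. This stands. A reader might infer that the protocol prescribes an unadjusted analysis; it does not. The point rests on what the protocol itself states: the equivalence claim, the pooling, and the inconsistent comparator.

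Second, the design already works against the bias through shared criteria, residence, representativeness and locality grouping. Monthly scheduled smears and daily temperature recording also make detection less dependent on care-seeking. This stands in part. Locality grouping is by clinic-visit group and only where possible, representativeness names no variable, and age is not balanced.

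Third, the study is labelled observational, and the dose, titre and waning analyses in items 1 to 4 of Section E do not need the pooled control. That is right and limits the severity. The malaria endpoints are nevertheless primary.

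Two further inferences should be resisted. One might add the 21-day dosing interval to the 40-day surveillance and say that the two sets were screened at least 61 days apart. This cannot be derived: the volunteers are recruited within the 40-day window, and the text does not give the interval from the second dose to its start. One might also call 66 v 18 a randomised comparison. The protocol states randomisation explicitly only for Stage 1.

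**Conclusion.** The concern holds in a limited form. B2.3 asserts equivalence for 73% of the controls on a ground that does not support it, and item 5 leaves the comparator ambiguous. The design measures reduce confounding but do not remove it, and Section E does not carry age, locality or net use into the malaria comparison.

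With no vaccine effect, rate differences of 10% to 50% between the volunteers and the trial cohort would produce apparent efficacy from about 7% to 27% in one direction and -8% to -57% in the other. These rate differences are assumptions. The documents show neither that a difference exists nor which way it would run, so a reader should not infer that the result will favour the vaccine. The group sizes assume that all Stage 2 subjects consent to follow-up. This should be fixed, but it does not undermine the study as a whole.

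**What to change.** 1. In B2.3, delete the statement that the untreated group is equivalent to placebo.
2. In Section E item 5, name one comparator and use it for both parasitaemia and episodes.
3. Make the main vaccine v pooled-control malaria comparison a regression adjusted for age and locality, with net, insecticide and spraying use as recorded at the first visit. Do not adjust this model for smear status at the first follow-up visit. For vaccinees that comes after both doses, and parasitaemia is itself an endpoint, so adjustment could remove a true effect.
4. Beside it, report vaccine v trial placebo (66 v 18) and placebo v untreated (18 v 48) as supporting analyses, with a note on their low precision. A non-significant 18 v 48 result should not be read as proof that pooling is safe.
5. In C(ii), name age band and locality as the variables on which the volunteers are to represent the consenting trial subjects.

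The cost is wording in B2.3, C(ii) and E and a little more analysis, since the covariates are already collected. Recruitment may be slightly slower, and the 66 v 18 estimate will be visibly imprecise.
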